### Intervention

After inclusion in the study, participants will be randomized into a conventional treatment group and a model treatment group. They will receive the following interventions at least 3 days. Conventional treatment group: latamoxef, 30 mg/kg q12h; model treatment group: latamoxef, 20 mg/kg, q8h. As steady-state plasma concentration of latamoxef will be reached after 18 h of dosing, the opportunistic blood sampling method will be used to collect samples for testing plasma drug concentration at initial stage of the treatment (18–72 h) (Table 3).

**TABLE 3 T3:** Study schedule of latamoxef RCT in EONS treatment.

Items	Study phases (The beginning of latamoxef treatment is set as 0 h)		
	Baseline (−3–−1 day)	Initial stage of treatment (18–72 h)	Before the end of latamoxef treatment
Informed consent form (ICF)	X		
Demographic information	X		
Medical history	X		
Diagnosis and determination of the treatment regimen	X		
Inclusion/exclusion criteria	X		
Get the random number	X		
Comorbid drug use	X	X	X
Weight	X	X	X
Vital signs^a^ and physical examination	X	X	X
Blood routine^b^	X	X	X
Blood culture	X	X	X
CRP and PCT	X	X	X
Liver and kidney function^c^ ^d^	X	X	X
Cerebrospinal fluid (CSF) examination (optional)^e^	X	X	X
Dose, frequency and time point of latamoxef administration		X	X
Detection of plasma latamoxef concentration		Random sampling point	
Sampling time of plasma samples		X	
Efficacy assessment			X
Adverse event assessment		X	X
Case report form (CRF)	X	X	X

a Vital signs include the temperature, blood pressure and oxygen saturation (SaO_2_).

b Blood routine tests include red blood cells, hemoglobin, white blood cells, and platelets.

c Liver function tests include alanine and aspartate aminotransferases, alkaline phosphatase level, total bilirubin, and gamma-glutamyl transferase.

d Kidney function tests include creatinine and blood urea nitrogen.

e CSF examination include CSF routine (characters, cells and Pandy’s test) and culture. This examination can be used when neonatologists suspect a patient has a neurological infection.

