#### Secondary Outcomes

This trial has five secondary outcomes:1) Rate of latamoxef treatment failure: the symptoms and laboratory indicators of infection persist or worsen after latamoxef treatment. Neonatologists have to increase of the dose of latamoxef, or add other antibiotics to the treatment with latamoxef, or stop latamoxef treatment and switch to other antibiotics.2) Duration of antibiotic therapy: the length of antibiotic therapy for EONS;3) Changes of white blood cell count (WBC), CRP and PCT: comparison of the changes of WBC, CRP and PCT at baseline, initial stage of treatment (18–72 h) and before the end of treatment (Table 3);4) Blood culture results during administration: comparison of blood culture results at baseline, initial stage of treatment (18–72 h) and before the end of treatment (Table 3);5) Incidence of adverse events (AE)s: monitoring and recording AEs during latamoxef therapy (Table 3).

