### Sample Size Estimates

According to our preliminary PPK study and dose simulation for latamoxef in neonates (Qi et al., 2019), 60.2% of neonates using conventional treatment regimen (30 mg/kg q12 h) reached 70% fT > MIC and 80.1% of neonates using model treatment regimen (20 mg/kg q8h) reached 70% fT > MIC with MIC of 2 mg/L, respectively. We conducted sample size estimation for superiority design by using PASS 15.0 (NCSS, Kaysville, Utah, United States). To achieve a statistical power of 80% (one-sided type 1 error of 5%), the calculated sample size of each treatment group was 57 patients per treatment group (114 in total) with the ratio of 1:1. Taking into account a 10% dropout rate, 64 patients per treatment group (128 in total) will be required.

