### Study Data and Statistical Analysis Plan

The procedures and contents of data collection for this trial are detailed in Table 2. Demographic information, diagnosis, clinical data and laboratory data at baseline will be recorded on electronic case report form (eCRF) platform provided by Six Yuan (Table 2). In addition, clinical data, laboratory data and AEs at every planed time point after initiation of treatment will also be recorded in this eCRF platform (Table 2). According to the data collection methods and standards formulated by project director and researchers, all data of eCRF platform will be recorded in a true, detailed and careful manner to ensure the authenticity of the data.

Statisticians, independent of all the other processes, will conduct the statistical analyses by using SPSS version 15.0 for Windows (Chicago, IL, United States). The statisticians will calculate the mean, standard deviation, median, minimum, maximum, lower quartile (Q1), upper quartile (Q3) for quantitative data and describe numbers and percentages for qualitative data (Wang et al., 2020). Comparisons between two groups will be conducted as following: t-tests or Wilcoxon rank-sum for normal or nonnormal ability distributions for quantitative data; chi-square test or Fisher’s exact test for qualitative data (Wang et al., 2020). Analysis for missing data performed on the intention-to-treat principle. For all analysis, *p* value < 0.05 will be considered statistically significant.

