To ensure that the finding of this trial can comprehensively reflect PD characteristics of latamoxef in EONS treatment, 70% fT > MIC will be used as the primary outcome indicator, and efficacy and safety indexes will be employed as the secondary outcome indicators. Because there’s no clinical evaluation of latamoxef in EONS treatment, the trial design is derived from other clinical trials about cephalosporin treatment or therapeutic decision conducted in children or neonates (Stocker et al., 2017; Wu et al., 2020). Rate of treatment failure, duration of antibiotic therapy, changes of inflammatory indicators, results of blood culture and incidence of AEs are commonly used indicators in efficacy and safety evaluation for anti-infective agents (Molyneux et al., 2011; Stocker et al., 2017). Since latamoxef is an oxacephem antibiotic that imparts time-dependent bactericidal effects, fT > MIC as a PD parameter is essential for efficacy evaluation of latamoxef. Although 40–50% fT > MIC is usually used in adult antimicrobial treatment, a goal of 70% fT > MIC is considered as a more conservative endpoint for avoiding treatment failure in immunologically immature neonates (Craig, 1995; Craig, 2001).

According to the bacterial susceptibility data of latamoxef in relation to the bacteria commonly observed in Chinese EONS patients, the MIC90 values of *E. coli* and *K. pneumoniae* were 1 mg/L and 2 mg/L (Cui Lan-Qing, 2016). Thus, 70% fT > MIC targets in two treatment regimens with MIC of 2 mg/L were applied as parameters in sample size calculation.

Our study had some limitations. First, since EONS patients often improve or recover at hospital discharge, follow-up is not designed in this trial. Hence our efficacy evaluation may miss some relapse situation after hospital discharge. Second, due to the few positive culture results and antimicrobial susceptibility results of bacteria in neonatal clinical practice, we chose 70% fT > MIC target with MIC of 2 mg/L in sample size calculation based on epidemiological microbiology data instead of individual microbiology. Finally, our study data are only from Chinese EONS patients in Beijing, limiting the generalizability to other populations and areas with different epidemiological microbiology data.

We hoped that our study can provide reliable data to support rational use of latamoxef in EONS treatment.

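### CRP and PCT changes are compared on an unnamed scale with an unadjusted test; if the change is the absolute difference, much of the power at end of treatment is lost once the markers fall by half or more

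*Protocol article*

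**What the plan says.** In the protocol article, Secondary Outcomes, item 3 is a "comparison of the changes of WBC, CRP and PCT at baseline", at 18–72 h and shortly before treatment ends. It does not say whether a change is an absolute difference, a percentage or a ratio. Table 3 schedules both markers at all three times ("CRP and PCT X X X"), so every infant should have a baseline value.

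The section Study Data and Statistical Analysis Plan assigns "t-tests or Wilcoxon rank-sum for normal or nonnormal ability distributions for quantitative data". It mentions no transformation and no baseline covariate, and sets one threshold for everything: "value < 0.05 will be considered statistically significant". The Discussion counts "changes of inflammatory indicators" among the usual efficacy and safety indicators for anti-infective agents. The article gives no spread, expected fall or effect size for CRP or PCT.

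**The concern.** CRP and PCT are positive concentrations, usually skewed, and tend to move proportionally. An absolute change is then the starting value times the fractional change, so an infant who starts high can show a large change with a modest proportional response. The plan foresees non-normal data, but its answer is to rank the same quantity, and the ranks still carry the baseline spread. That spread may be wide: the diagnostic criteria include suspected cases resting on maternal risk factors as well as culture-proven infection.

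At stake is whether a real difference in how fast inflammation resolves would be visible at the end of treatment. The trial is sized for the pharmacokinetic target, so these markers have little power to spare.

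**Working it through.** **Inputs from the article.** The number per arm comes from Sample Size Estimates: "the calculated sample size of each treatment group was 57 patients per treatment group (114 in total) with the ratio of 1:1". It was calculated for the primary outcome and is used here only as the number analysed. Standard formulas for that calculation give 63–65 per arm rather than 57; that is a separate matter and does not bear on this point. The 0.05 level is taken as two-sided, since the article does not say.

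**Inputs assumed.** Everything about the markers: log-normal distribution, spread, correlation between baseline and end value, size of the fall, and regimen effect.

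**Step 1, algebra.** With baseline b and end value e = r·b, the absolute change is e − b = b(r − 1). Illustration with invented values:
- 80 to 32: 80 × (0.4 − 1) = −48, a 60% fall.
- 10 to 1: 10 × (0.1 − 1) = −9, a 90% fall.

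On the absolute scale the first infant ranks as the better responder.

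**Step 2, simulation grid.** 57 per arm, two-sided 5%, log-SD 1 at both times, correlation 0.3, 0.5 or 0.7, end values in one arm truly 40% lower (ratio 0.6), no assay limit, 1,500 runs per cell. Ranges run over the three correlations. The second column is the Spearman correlation of the absolute change with baseline; the others are power.

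| Median end/baseline | Correlation with baseline | Rank-sum, absolute change | Rank-sum, end value | Rank-sum, log ratio | Log model with ln(baseline) |
|---|---|---|---|---|---|
| 0.10 | −0.98 to −0.99 | 6–7% | 75–76% | 61–92% | 81–97% |
| 0.25 | −0.92 to −0.94 | 13–14% | 76–78% | 61–93% | 81–97% |
| 0.33 | −0.88 to −0.90 | 16–22% | 76–77% | 61–92% | 81–97% |
| 0.50 | −0.79 to −0.80 | 27–41% | 75–77% | 60–92% | 81–97% |
| 0.75 | −0.64 to −0.70 | 38–65% | 75–76% | 60–92% | 81–96% |
| 1.00 | −0.48 to −0.61 | 48–81% | 75–76% | 61–92% | 82–96% |

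Share of attainable power lost, at correlation 0.5:
- fall to 0.25: (87.8 − 13.9)/87.8 = 84%;
- fall to 0.50: (88.3 − 33.7)/88.3 = 62%.

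With end/baseline 0.75–1 the loss over the three correlations is about 15–55%. A t-test on the absolute change does worse than the rank-sum test: 7.5% against 14% at a fall to 0.25 and correlation 0.5 (3,000 runs).

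**Step 3, a second simulation.** With a true ratio of 0.63, a fall to 25–40% of baseline and no assay limit, the rank-sum test on the absolute change has 13–38% power, and the log model with ln(baseline) 80–87%.

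**Step 4, no regimen effect.** The rank-sum test on the absolute change rejected in 6.1% and 5.1% of trials in two separate runs, near the nominal 5%.

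**Step 5, assay limit.** If an end value is set to a limit L, the log ratio is ln(L) − ln(b), again ordered by baseline. With median baseline 10, limit 3 and a fall to 25%, about 61–67% of end values sit at the limit. Power is then 18–23% for the log ratio, 8–9% for the absolute change and 30–59% for the rank-sum test on end values. With limit 5 it is 10–11% for the log ratio and 22–49% for end values. Across all 32 scenarios of the simulation in step 3, the log model with ln(baseline) matched or beat the absolute change, the log ratio and plain end values to within about one percentage point.

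**The case against.** The strongest reply is that the article never says the change is an absolute difference. Baseline is itself listed as a comparison time, where a change from baseline has no content, and item 4 uses the same construction for blood cultures, where it can only mean results visit by visit. If values at each visit are compared, the rank-sum test keeps 75–78% power in the grid above. This stands in part: absolute change is the plain reading of the word, but it is inferred. The visit-value reading does not remove the point, since unadjusted end values still fall short of 81–97% there. In a different simulated structure (end value equal to baseline times an independent random ratio, typical fall to 40%, true reduction 33%) they reach only 24–62%, against 56–95% for a t-test on the log ratio.

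A second reply is that scale and covariates belong in a full analysis plan, which is not shown and may already settle them. That is fair as to what is left unsaid. What the article does state is an unadjusted two-group test on changes, and that choice can be judged.

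Third, every marker input is assumed. This stands. A reader might infer that the plan throws away most of its power whatever happens; the documents do not support that, because the loss depends on a substantial fall and is modest when markers barely move or are still rising.

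A reader might also infer that the comparison would mainly reflect how ill the infants were at entry. Randomisation balances baseline on average and type I error stays near 5%, so baseline spread adds noise and does not favour either arm. Nor does the article say that a null marker result would be taken as equal efficacy.

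**Conclusion.** The point holds conditionally. The article fixes an unadjusted test on a change whose scale it does not name. If that change is the absolute difference and the markers fall by half or more, more than half of the attainable power at end of treatment is lost in the grid, and at least about three quarters when they fall to a third or less. These sizes rest on log-normal markers, the assumed spreads and correlations, and a regimen effect of roughly 37–40% (ratio 0.60–0.63), none of which the documents supply.

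Comparing visit values instead is generally less powerful than adjusting for baseline; that advantage goes when most end values sit at the assay limit. The consequence is imprecision on one of five secondary outcomes. The primary outcome is unaffected. It is still worth changing, because a better analysis is available on data already scheduled.

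**What to change.** In Secondary Outcomes item 3 and in Study Data and Statistical Analysis Plan, state for CRP and PCT:

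- At each on-treatment visit, ln(value) is analysed in a linear model with treatment arm and ln(baseline) as covariate, in place of an unadjusted test on the change.
- The result is reported as the ratio of geometric means between arms with a 95% CI.
- Values below the assay limit are set to one fixed value, the same in both arms. If many values are at the limit, a rank-based sensitivity analysis is added.

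Do not substitute an unadjusted log ratio, for the reason in step 5 of the working. If a fuller analysis plan already specifies this model, only the article's wording needs aligning.

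Cost: wording only, with no new samples or visits. The effect reads as a ratio instead of a difference in concentration, and values at the assay limit need a substitute.

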### Safety and AE Monitoring

In this trial, safety will be monitored, including AEs, serious AEs, and withdrawals due to AEs. The safety indexes are mainly composed of the routine blood, liver function, kidney function, coagulation function and vital signs. AEs of latamoxef mainly include anaphylaxis (such as rashes, urticaria, and itching), gastrointestinal reactions (such as vomiting, diarrhea and abdominal pain), and other latamoxef associated AE (such as anaphylactic shock, elevated levels of aminotransferases and serious bleeding).

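### Adverse events are counted only while latamoxef is given, so crude incidences can rest on unequal windows; Table 3 should also say that AE recording starts at the first dose

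*Protocol article*

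**What the plan says.** Under Secondary Outcomes, item 5 of the protocol article gives AE incidence as "monitoring and recording AEs during latamoxef therapy (Table 3"). The counting period is thus the period on latamoxef.

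The length of that period is left open. The Intervention section gives a minimum of 3 days and no maximum. Secondary outcome 1 counts a change from latamoxef to other antibiotics as one form of treatment failure. Safety and AE Monitoring provides for withdrawals because of AEs. Secondary outcome 2 compares the length of antibiotic treatment between arms. The limitations paragraph of the Discussion says that no follow-up is planned and gives only missed relapse as the consequence.

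Table 3 fixes its clock with "The beginning of latamoxef treatment is set as 0 h". Its first on-treatment column is "Initial stage of treatment (18–72 h"). The row "Adverse event assessment" is marked in that column and in the end-of-latamoxef column only. Study Data and Statistical Analysis Plan says the eCRF will take "laboratory data and AEs at every planed time point after initiation of treatment". The same section compares qualitative data between the two groups by chi-square or Fisher's exact test.

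**The concern.** AE incidence is the only safety item among the listed outcomes. As defined, each infant is observed for AEs for as long as latamoxef continues, and response partly decides that. An arm whose infants respond slowly stays on the drug longer and has more time to accumulate events. An arm with more early switches for failure is observed for less time and can look safer. A crude comparison of proportions cannot separate either effect from a true difference in risk.

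The second point is one of wording. The outcome covers therapy from its first hour, yet the schedule it refers to shows no AE mark before 18 h. The only reason given for 18 h is steady state for drug sampling, which is not a safety reason. Safety and AE Monitoring states that "AEs of latamoxef mainly include anaphylaxis (such as rashes, urticaria, and itching") and goes on to name anaphylactic shock, so the first doses should plainly lie within the recording period.

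**Working it through.** The article states no figure for AE incidence, so there is none to reproduce. The check has two parts.

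**1. Effect of unequal windows**

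Inputs from the article: counting ends with latamoxef; minimum 3 days, no maximum; qualitative outcomes compared as proportions. Inputs assumed, because the article gives neither: a constant AE hazard *h* per day, identical in both arms, and mean latamoxef durations *t* by arm.

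Formula: incidence = 1 − exp(−*h* × *t*).

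Worked case, *h* = 0.05, 5 v 7 days:
- shorter arm: 1 − exp(−0.25) = 22.1%
- longer arm: 1 − exp(−0.35) = 29.5%
- difference: 7.4 points, with no difference in risk.

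| Hazard per day | Days | Incidences | Gap (points) |
|---|---|---|---|
| 2% | 5 v 7 | 9.5% v 13.1% | 3.5 |
| 5% | 5 v 6 | 22.1% v 25.9% | 3.8 |
| 5% | 5 v 7 | 22.1% v 29.5% | 7.4 |
| 8% | 5 v 7 | 33.0% v 42.9% | 9.9 |
| 10% | 5 v 7 | 39.3% v 50.3% | 11.0 |
| 5% | 3 v 3 | 13.9% v 13.9% | 0 |

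Gaps are taken before rounding. For 5 v 7 days the artefact runs from about 4 to 11 points over hazards of 2% to 10% per day. It is zero when durations are equal.

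Under the same model, a common 72 h window gives 1 − exp(−0.15) = 13.9% in both arms, and the event rate is 5 per 100 latamoxef-days in both. Each supplementary measure therefore removes the artefact when the hazard is constant.

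Stopping early does not always shorten the window in a way that matters. An infant withdrawn because of an AE already counts as having one; only further events are lost. Stopping for failure before any AE is what truncates the any-AE proportion.

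**2. The first 18 hours**

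The interval is 18/72 = 25% of the minimum course. Before 18 h, the q12h schedule gives doses at 0 and 12 h (2 of the 6 in 72 h), and the q8h schedule gives doses at 0, 8 and 16 h (3 of 9). That is one third in each arm. The interval is the same clock time in both arms, so it does not make the windows unequal.

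Side by side, the outcome definition includes 0 to 18 h. The schedule and the eCRF sentence tie entry to planned time points, and none is planned before 18 h. The texts are compatible if the 18 to 72 h assessment looks back to 0 h, but the article does not say that it does.

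**The case against.** The strongest reply on windows is that on-treatment counting is a legitimate choice, that the article shows no reason to expect different latamoxef durations, and that every hazard and duration above is assumed. The constant-hazard model may also overstate the effect: if reactions cluster at the first doses, extra late days add less. A condensed article may leave exposure adjustment to a fuller plan, and its line on chi-square and Fisher tests is generic. Much of this stands. The size is illustrative, and the absence of an exposure-adjusted rate is not in itself a fault. What remains is something the article does state: the outcome's window ends with a treatment whose length is open and linked to response, in a trial that itself compares length of antibiotic treatment between arms.

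On Table 3, a reader might infer that reactions before 18 h go unrecorded. The documents do not support that. The outcome covers all of latamoxef therapy, the safety section sets no time limit, and the columns read naturally as assessment points that look back. Read as counting windows, they would also lose events between 72 h and the final assessment, which is plainly not intended.

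A reader might likewise infer that dose times before 18 h are lost to the pharmacokinetic calculation, because the administration row has the same gap. That row sits beside the sampling-time row in the 18 to 72 h column, and a sample drawn soon after 18 h can be interpreted only with the earlier doses. A dosing history back to 0 h is the natural reading. These objections stand, and they reduce the Table 3 point to a clarification.

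**Conclusion.** The point holds in limited form. Tying AE incidence to time on latamoxef and comparing crude proportions allows a difference to appear at equal underlying risk. The illustrative size is 7.4 points at an assumed 5% per day and 5 v 7 days, and about 4 to 11 points over 2% to 10% per day. It vanishes if the arms are treated equally long. The article does not show that durations will differ or in which direction, so this is an exposure to bias and not a demonstrated bias.

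The missing 0 to 18 h mark is a separate matter of consistency. It neither excludes early events nor causes unequal windows. The outcome definition, Table 3 and the eCRF sentence need to say the same thing. Both parts are worth correcting mainly because correction is cheap; neither touches the primary comparison.

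**What to change.** 1. In Table 3, state that the AE row and the row for dose and time of administration run from the first dose (0 h), with the 18 to 72 h assessment covering everything since 0 h.
2. In secondary outcome 5, keep whole-course AE incidence, so that later events stay in the report, and add:
   - the proportion of infants with at least one AE from first dose to 72 h, counted in every randomised infant whether or not latamoxef has stopped;
   - whole-course AEs per 100 latamoxef-days, by arm.

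The two additions complement each other. The 72 h proportion gives both arms the same window but omits later events. The rate uses the whole course but averages over it, so it can favour the longer-treated arm if events cluster early.

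Cost: a note to the schedule, a sentence or two in the outcome definition and slightly more analysis. AEs must still be recorded to 72 h in the few infants who stop latamoxef earlier. The infants are recruited as inpatients, so no extra visit or test should be needed.
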